### Materials and methods: Phase III

Objective 3: Understand adherence in first-line and second-line ART patients who are virologically suppressed and those who are not virologically suppressed in selected urban and rural communities.

#### Study design

The study will employ a qualitative study design approach. Active patients from phase I and II (in both urban and rural settings) will be invited to participate in the in-depth interviews (IDIs) to explore factors including (but not limited to) treatment history, current use of ART, treatment regimen, financial/economic factors, risk behaviours (substance use), psychosocial characteristics cultural beliefs, spirituality and), relationship related factors (treatment support), community level factors (societal norms, stigma, discrimination, disclosure), and policy level factors (understanding/awareness of HIV/ART policies and treatment guidelines).

#### Study setting

This study will be conducted in seven health facilities in the city of Johannesburg region F in Gauteng Province and one in Limpopo Province (Ndlovu Medical Centre).

The seven health facilities in the city of Johannesburg include:

**Primary Health Care**: Jeppe Clinic, Malvern Clinic, Rosettenville Clinic, Yeoville Clinic**Community Health Centre**: Hillbrow Community Health Center (HCHC)**Hospitals**: Charlotte Maxeke Johannesburg Academic Hospital (CMJAH) and South Rand Hospital (SRH)

#### Sampling/Sample size

In this study, purposive sampling of patients currently taking ART will be employed to ensure maximum variation among the study sample. We will ensure a diverse sample by considering viral load status (suppressed and unsuppressed time on ART, age (18 years and older), sex (both males and females) and education. Sample size will depend on when saturation is reached; we anticipate that a maximum of 60 IDIs will be conducted across both study settings and viral load status groups (suppressed and unsuppressed). An anticipated number of study participants to recruit is 15 per viral load status group in each study setting (making a total of 30 participants in each study setting).

#### Data collection

Patients for this phase will be contacted using the contact information that they provided for their facility records or databases used in phase I and II. IDIs will be conducted following a semi-structured interview guide. The guide will comprise open-ended questions covering treatment history, current use of ART and multilevel factors derived from the socio-ecological framework. This will include individual level factors including treatment-related factors (ART regimen, use of non-ART medication), financial and economic factors risk behaviours (substance use), psychosocial factors (cultural beliefs, spirituality), interpersonal-level factors (relationship between patients and treatment supporters or caregivers, such as intimate partners, family members, friends and health care workers), community level factors (social norms regarding HIV and ART, HIV-related stigma and discrimination, HIV-status disclosure), health-system factors (access to HIV and ART services including adherence counselling), and policy level factors (HIV testing and treatment guidelines and policies). Additional probes will be included for each question to promote sharing of detailed information regarding their perspectives and experiences, and to ensure clarification if required (see S1 Appendix study codebook and S2 Appendix interview guide). All IDIs will be audio recorded and transcribed verbatim. Transcripts will be translated into English.

*Deductive themes*. Deductive themes may include treatment history, current use of ART, treatment regimen, financial/economic factors, risk behaviors (substance use), psychosocial characteristics cultural beliefs, spirituality and), relationship related factors (treatment support), community level factors (societal norms, stigma, discrimination, disclosure), and policy level factors (awareness of HIV/ART policies and treatment guidelines).

#### Data analysis

Transcripts will be imported and analysed using NVIVO. Data coding will be undertaken using deductive (top down) and inductive approaches (bottom up) [54]. A deductive approach is driven by researchers’ analytic interest in the study, reflecting the broad issues addressed in the interview guide. An inductive approach is used to identify the detailed themes related to the overarching issues that can be identified in the data [54]. Thematic analysis will be used, which is a method for identifying, analysing, and reporting patterns (themes) within data [54,55]. Transcripts will be read while noting similar topics that will be grouped into major topics or themes. Data will be analysed as transcripts become available shortly after interviews are conducted. This will ensure the early identification of emerging themes and assist in the identification of data saturation. Analysis of the IDIs will follow the phases of thematic analysis which are familiarization, generating initial codes, searching for themes, reviewing themes and interpretation [54]. Familiarization (getting grounded into the data collected), will be achieved by reading the transcripts and field notes repeatedly. During the process of generating codes, key emerging ideas and words from the familiarization phase will be recorded from which we will search, identify, and review themes, concepts, categories, and sub-categories. This will be done in keeping with socio-ecological framework, views and experiences that persist from the data. Finally, factors that influence adherence to ART will be identified and grouped into main categories. Analysis will be guided by the codebook which will be developed by the study team post familiarization with the data. There will be multiple independent coders to ensure the reliability of the coding.

### Materials and methods: Phase IV

Objective 4: Assess and compare adherence intervention strategies for the chronic conditions of HIV, hypertension and DM which have been tested and implemented in sub-Saharan Africa (Title: Adherence strategies and interventions for selected chronic conditions in sub-Saharan Africa: a systematic review and meta-analysis) (see S4 Appendix Systematic review protocol).

#### Study design

This systematic review will be designed and reported according to the PRISMA [56] (see S5 Appendix PRISMA checklist), following the registered protocol (CRD42019127564) on the international prospective register of systematic reviews, Prospero [57] (see S4 Appendix Systematic review protocol). The study will use PICO criteria as the search strategy tool.

A systematic review on the impact of treatment adherence interventions in chronic conditions (HIV, hypertension, DM) in sub-Saharan Africa will be conducted to provide context to adherence in sub-Saharan Africa. In this region, HIV remains the leading cause of death more especially in the young and middle-aged adults. However, the burden of non-communicable diseases (NCDs), particularly DM and hypertension, has increased rapidly in recent years [58–60].

#### Study setting

All information from sub-Saharan Africa only will be included for the systematic review.

#### Sampling/Sample size

All interventions described as chronic conditions adherence interventions (HIV/ART, hypertension, DM). Inclusion in the systematic review will be dependent on the criteria set out in the systematic review protocol [57] and reported using the PRISMA reporting guidelines.

#### Data collection

A pre-defined data sheet will be developed for data extraction. The tool will include (but not be limited to): reference (author, title), year of publication, setting or location, sample size, intervention description, participants receiving adherence (in case of comparison) (see S1 Appendix study codebook). The form/tool will be tested before conducting the final searches. One reviewer will conduct all the data extraction while a second reviewer will be responsible for data quality assurance on the extraction and also conduct full text review of the included material.

We will search using several electronic databases. These will include PubMed/Medline, Web of Science, Google Scholar, Scopus, and CINAHL. If necessary, we will contact study authors and request more information on individual studies. Citations and bibliographies of records will be reviewed to identify additional relevant material.

The basic search terms included will be:

*“Chronic conditions”* OR *“hypertension”* OR *“high blood pressure”* OR *“blood pressure”* OR *“arterial hypertension”* OR *“mellitus diabetes type I”* OR *“mellitus diabetes type II”* OR *“Diabetes”* OR *“Sugar”* OR *“HIV”* OR *“Antiretroviral Therapy”* OR *“Antiretroviral Treatment”* OR *“ART”* OR *“ART Programs”* OR *“ART Programmes”* AND *“adherence”* OR *“compliance”* AND *“interventions”* OR *“strategies”* OR *“odds ratio”* OR *“risk ratio”* OR *“evaluation”* OR *“impact”* OR *“effectiveness”* OR *“outcome”* AND *“sub-Saharan Africa”* OR *“sub Saharan Africa”* OR *“sub-Saharan African”* OR *“sub Saharan African”* OR *“Africa”* (Table 1).

**Table 1 pone.0261107.t001:** Methodological aspect of the systematic review.

Criteria for study inclusion	Components details
Population (P)	Patients with selected chronic conditions (HIV, hypertension, dDM) in sub-Saharan Africa
Intervention (I)	All interventions listed/described as adherence interventions or strategies for the conditions of HIV, hypertension, DM
Comparisons (C)	Standard of care and other adherence interventions reported on in the review
Outcome (O)	The included studies should report any measurement of adherence to chronic conditions—primarily, effects on adherence behaviour and the changes in health outcomes. There is no preferred measurement for reporting; should there be adequate statistical reporting, a meta-analysis will be considered.
Setting	All studies from sub-Saharan Africa only will be considered for the review.
Language	There will be no language restrictions.
Date	There will be no date/time restrictions.
Publication status	All the documented studies will be considered and included for review. This includes peer reviewed (i.e., papers, manuscripts, and abstracts).
Method	The study will be designed and reported according to PRISMA. PICO will be used as a search strategy approach. This study will describe reported adherence programmes and strategies. There will be a focus on behaviour change techniques used or reported changes in process outcomes of adherence programmes and methods of implementation for HIV, hypertension and /or DM.
Search strategy and selection procedure	We will search using several electronic databases. These will include: PubMed/Medline, Scopus, CINAHL, Web of Science and Google Scholar.
Search terms	(chronic conditions OR hypertension OR high blood pressure OR blood pressure OR arterial hypertension OR mellitus diabetes type I OR mellitus diabetes type II OR Diabetes OR Sugar OR HIV OR Antiretroviral Therapy OR Antiretroviral Treatment OR ART OR ART Programs OR ART Programmes) AND (adherence OR compliance) AND (interventions OR strategies OR odds ratio OR risk ratio or evaluation OR impact OR effectiveness OR outcome) AND (sub-Saharan Africa OR sub Saharan Africa OR sub-Saharan African OR sub Saharan African OR Africa)

The search terms will be adjusted to suit the database being searched. An inventory with the database searched, the corresponding search criteria used, the date when the searches were conducted, and the results will be maintained. A second reviewer will run the searches separately for comparison. The strength of the body of evidence (quality of evidence), the risk of bias and magnitude of effect will be rated and assessed using Grading of Recommendations Assessment, Development and Evaluation (GRADE) [61,62].

*Outcome*. The primary outcome will be adherence to antiretroviral therapy, defined as the proportion of patients meeting the defined adherence criteria. The secondary outcome will be proportion of patients achieving viral suppression, as defined by the study. Outcome (and impact) measures will be reported in terms of changes in the prevalence or reduction in the relative risk. Should there be adequate statistical reporting, a meta-analysis will be considered [63].

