#### Strengths and limitations

To our knowledge this will be the first study using a social-ecological perspective and a convergent parallel mixed method design to report on combination ART in South Africa. Combining quantitative and qualitative data from public health settings, a controlled environment, the patient perspective and evidence from the region will enable us to make recommendations for a comprehensive, acceptable, and appropriate adherence strategy for the country.

The study presents a fewlimitations. The study will be conducted in a total of eight health facilities (seven of over 120 health facilities in one South African metropolitan municipality (urban setting) and one facility in a rural setting). Therefore, findings may not be generalizable to other municipalities and districts in South Africa, or to other country settings. Furthermore, although there are efforts to ensure good quality of data by the South African Department of Health, supporting partners and research staff, secondary data are subject to quality issues, due to data inconsistencies and missing data. Other potential predictors of adherence, such as disclosure, stigma, and self-reported adherence, will be assessed through a standard questionnaire. This may lead to reporting bias (memory and social desirability biases). Policy-level factors might not probe for relevant factors due to how this study is designed (with it focus on the individual’s awareness of health policies and guidelines which is insufficient to fully assess policy-level factors).

In conclusion, our study will demonstrate how an existing socio-ecological conceptual framework can be used as a tool to provide guidance regarding facilitators and barriers to ART adherence. By populating this framework through secondary data analysis, participant interviews of PLHIV who are taking ART and a systematic review comparing adherence intervention strategies for the chronic conditions, this mixed method study will provide evidence on factors affecting treatment adherence at different socio-ecological levels and guide context-specific intervention strategies to improve ART adherence. We believe that the use of our study results to strengthen adherence intervention will subsequently improve health outcomes and decrease the number of patients switching to complex treatment such as second-line and third-line regimens.

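### Phase IV plans pooled adherence risk ratios with any measure admitted and none preferred, and its stated sensitivity analyses cannot show whether a pooled benefit depends on self-report

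*Protocol article*

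**What the plan says.** All references are to the protocol article, Materials and methods: Phase IV.

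- **Eligibility (Data collection, Table 1, Outcome row).** "The included studies should report any measurement of adherence to chronic conditions". The row goes on: "There is no preferred measurement for reporting", and then makes meta-analysis conditional on adequate reporting.
- **Comparator (Table 1).** "Standard of care and other adherence interventions reported on in the review".
- **Primary outcome (Data collection, Outcome).** "The primary outcome will be adherence to antiretroviral therapy, defined as the proportion of patients meeting the defined adherence criteria". No method of measurement is attached.
- **Secondary outcome.** "The secondary outcome will be proportion of patients achieving viral suppression, as defined by the study".
- **Pooling (Data analysis).** Unadjusted RRs are calculated where needed, and a random-effects model gives summary RRs with 95% confidence intervals.
- **Robustness (Data analysis).** Two checks are named: risk difference in place of RR, and fixed in place of random effects.
- **Related safeguards.** Risk of bias is to be rated with GRADE, and the section plans a descriptive comparison of the kinds of assessment and outcome measure used.

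**The concern.** Self-report, pill count and more objective measures do not carry the same risk of bias. The article treats them as distinct elsewhere: Phase II defines self-reported adherence, pill count and virological failure as separate outcomes, each with its own rule.

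In Phase IV the comparison is with standard of care or with another adherence intervention. Strategies that the article names in its Research gap section, such as targeted counselling and adherence clubs, are likely to be evident to the patient. A coached patient may have more reason to report good adherence. If so, the error in self-report differs between arms and can look like a treatment effect.

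Phase IV is meant to compare strategies and to feed recommendations for roll-out in South Africa. If some strategies were evaluated mainly by self-report, part of their apparent advantage could come from the measure. The stated sensitivity analyses would not reveal this.

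**Working it through.** The article gives no effect size, power or expected number of studies for Phase IV, so there is no plan figure to reproduce. Every numerical input below is an assumption, used to show direction and rough size.

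**1. One self-report study, simple version.** Assume true adherence of 0.70 in both arms, no over-reporting in controls, and 5 to 10 percentage points of over-reporting under intervention.
- RR = 0.75/0.70 = 1.07
- RR = 0.80/0.70 = 1.14
- The true RR is 1.00.

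**2. One self-report study, misclassification version.** Let p be true adherence in both arms. All adherent patients report adherence. Non-adherent patients falsely report it with probability f0 (standard of care) or f1 (intervention).
- Observed proportion = p + (1 − p)f
- Spurious RR = [p + (1 − p)f1] / [p + (1 − p)f0]
- With p = 0.7, f0 = 0.2, f1 = 0.4: 0.82/0.76 = 1.08; risk difference 0.06.
- Over p = 0.5 to 0.8, f0 = 0.2 or 0.4, and f1 larger by 0.1 or 0.2: RR 1.02 to 1.17, risk difference 0.02 to 0.10.
- The chance of a falsely significant benefit with 150 per arm (two-sided 0.05, normal approximation) is about 7% to 52%, against a nominal 2.5% in that direction.

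**3. A mixed pool.** Take ten equal trials of 150 per arm with p = 0.7, f0 = 0.2, f1 = 0.4. Let s be the share of weight from self-report, the other trials having RR = 1.
- Pooled RR = exp[s × ln(0.82/0.76)]
- Standard error of log RR = √{[0.24/(150 × 0.76) + 0.18/(150 × 0.82)]/10} = 0.019

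| Self-report share of weight | Pooled RR (approx. 95% CI) |
|---|---|
| 25% | 1.02 (0.98 to 1.06) |
| 50% | 1.04 (1.00 to 1.08) |
| 75% | 1.06 (1.02 to 1.10) |
| 100% | 1.08 (1.04 to 1.12) |

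These intervals use one standard error throughout and no between-study variance. A trial with 0.70 in both arms has log-RR variance 2 × 0.30/(150 × 0.70) = 0.0057, against 0.0036 for a self-report trial. The intervals for mixed pools are therefore somewhat too narrow, and the 50% row, which only just touches 1, should not be read as significant.

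**4. Equal over-reporting.** If f1 = f0 and there is no true effect, the RR is 1.00. With a real effect of 0.70 against 0.60 (RR 1.17):
- f = 0.2: 0.76/0.68 = 1.12
- f = 0.4: 0.82/0.76 = 1.08

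The bias then runs towards 1.

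**5. What the planned checks can see.** In the example in step 2, the RR (1.08) and the risk difference (0.06) are both shifted from the null, because both come from the same two proportions. Fixed and random effects weight the same study estimates differently. If all studies carried the same bias, the two models would agree on the wrong value. Neither check separates studies by type of measure.

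**The case against.** The strongest case against is that this is a condensed article. The review has its own registered protocol, given as S4 Appendix, and the article defers inclusion criteria to it. An extraction hierarchy, subgroups by measure and a named study-level risk-of-bias tool are commonly left to such a document. That stands for the risk-of-bias tool, which is not part of this point. It does not fully answer the rest: the absence of a preferred measure is stated outright in Table 1, and the sensitivity analyses are stated outright in Data analysis.

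Several stronger readings are tempting and are not supported:

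- *That all measures will be pooled on equal terms in one RR.* The Table 1 sentence is mainly an eligibility rule, and it makes meta-analysis conditional on adequate reporting. Data analysis does plan summary RRs, but nowhere says that all measures enter a single one.
- *That the extractor may pick any measure a study reports.* The article does not say how multiple measures are handled, and it provides for a predefined, tested sheet and a second reviewer.
- *That the authors concede the bias for the review.* The sentence under Strengths and limitations, "This may lead to reporting bias (memory and social desirability biases"), concerns the study's own questionnaire. The mechanism carries over; the admission does not.
- *That the pooled RR is biased away from 1.* This needs over-reporting that differs between arms. Where both arms receive an adherence intervention, the argument for such a difference is weaker.

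The existing safeguards also count. Viral suppression, the GRADE rating and the descriptive comparison of assessments would all help a careful reader. None of them splits the pooled adherence estimate by measure.

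**Conclusion.** The point holds in a limited form. The plan admits any adherence measure, prefers none, provides for pooled RRs on the primary outcome, and names only robustness checks that cannot tell whether a benefit depends on self-report.

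The possible size is modest but relevant: an RR of about 1.07 to 1.14 in a single self-report study with no true effect, and about 1.02 to 1.06 in a pool where self-report carries a quarter to three quarters of the weight. These figures rest on assumed adherence and assumed differential over-reporting. They also rest on the inference that patients know which intervention they receive, and the share of self-report studies is unknown. The result is a risk to interpretation that should be addressed, not a demonstrated bias.

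**What to change.** Keep all adherence measures eligible, so that no study is lost from the review. Then:

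1. Add a field for type of measure to the extraction sheet, which is still to be developed.
2. State in advance a rule that takes one measure per study for the pooled analysis and favours the more objective one where several are reported. The exact ordering is for the review team to settle.
3. Add to Phase IV Data analysis a pooled RR stratified by objective versus self-reported measure, or at least a sensitivity analysis that excludes self-report.
4. Read the adherence result beside the viral suppression result already planned, from the same studies where both are reported.

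Whether the objective stratum should be the primary summary is debatable and need not be imposed.

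The cost is one extraction column, a short amendment to the review protocol, and fewer studies with wider intervals within each stratum. Check S4 Appendix first. If it already sets a rule or a stratified analysis, the article only needs its Table 1 and Data analysis text brought into line.

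### As printed, the Phase IV search requires a regional word and lists no country names, so it risks missing studies that name only their country and tilts retrieval towards South Africa

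*Protocol article*

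**What the plan says.** The setting row of Table 1 (protocol article, Phase IV, Data collection) defines the scope: "All studies from sub-Saharan Africa only will be considered for the review". The same table sets no language or date restriction.

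The article prints the search string twice, in the running text and in the last row of Table 1. The running text introduces it with "The basic search terms included will be". Both versions use the same geographic terms: four spellings of the regional name and its adjective, plus the single word Africa. In Table 1 the brackets make the structure plain, and the final block is "AND (sub-Saharan Africa OR sub Saharan Africa OR sub-Saharan African OR sub Saharan African OR Africa". Neither version contains a country name.

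Three other statements bear on retrieval:

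- Databases: "These will include PubMed/Medline, Web of Science, Google Scholar, Scopus, and CINAHL".
- Adaptation: "The search terms will be adjusted to suit the database being searched". A second reviewer also runs the searches separately.
- Supplementary searching: "Citations and bibliographies of records will be reviewed to identify additional relevant material".

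The sections on study design and sample size refer to a registered review protocol, reproduced as S4 Appendix, which is not among the documents at hand.

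**The concern.** A geographic filter should let through every record that meets the setting criterion. This one lets through records that use a regional word. The two sets differ: a paper whose title and abstract place it in Uganda or Malawi, without mentioning the continent, is eligible but does not satisfy the printed string.

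The loss is also uneven. South Africa is the country whose usual name contains the word Africa, so a record can satisfy the block simply by naming it. Records from other countries need an additional regional word.

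This matters because Phases I to III are set entirely in South Africa. Phase IV is the only part of the study that brings in evidence from elsewhere, and Strengths and limitations relies on it as the regional evidence behind the recommendations. Its account of limitations does not mention the search. Nor can the analysis repair the problem: the fixed-effects re-run and the risk-difference sensitivity analysis use only the studies that were retrieved.

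**Working it through.** The plan states no figure for search yield or sensitivity, so there is nothing to reproduce. The check has a logical part and an illustrative part.

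**1. The string applied as text.** Inputs: the four AND-joined blocks of Table 1 (condition, adherence, intervention or evaluation, geography), matched as whole words. The test record was a constructed title, 'Effectiveness of an HIV treatment adherence programme in [country]', which satisfies the first three blocks. It was completed with each of 49 country names (an assumed list).

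- Titles passing all four blocks: 1 of 49, South Africa.
- Titles failing: 49 - 1 = 48, all on the geographic block alone.
- Central African Republic is among the failures, because African by itself is not a term.

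By the same rule, a record that says only South African, or gives only a South African city or province, also fails. The test shows how the logic works. It does not estimate real retrieval, since the constructed records have no abstract, keywords or indexing.

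**2. What the tilt could look like.** Let *s* be South Africa's true share of eligible studies, *r* the fraction of other countries' eligible records that are retrieved, and *q* the fraction of South African ones retrieved. The documents give none of these; all are assumptions.

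Share among retrieved = *s q* / (*s q* + (1 - *s*) *r*)

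With *q* = 1, the formula reduces to *s* / (*s* + (1 - *s*) *r*):

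| True share *s* | *r* = 0.3 | *r* = 0.5 | *r* = 0.7 | *r* = 0.9 | *r* = 1 |
|---|---|---|---|---|---|
| 20% | 45% | 33% | 26% | 22% | 20% |
| 30% | 59% | 46% | 38% | 32% | 30% |
| 40% | 69% | 57% | 49% | 43% | 40% |

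For *s* = 25%:

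- *r* = 0.8: 0.25 / (0.25 + 0.75 × 0.8) = 0.25 / 0.85 = 29%.
- *r* = 0.5: 0.25 / (0.25 + 0.75 × 0.5) = 0.25 / 0.625 = 40%.

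If some South African records are lost too, the tilt shrinks. With *s* = 25%, *r* = 0.5 and *q* = 0.9, the share is 0.225 / (0.225 + 0.375) = 0.225 / 0.600 = 37.5%, against 40% with *q* = 1. If *q* = *r*, the share stays at 25%, although studies are still missed. If both equal 1, there is neither loss nor tilt.

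**The case against.** The strongest reply is that the article is a condensed account. It calls these terms basic, refers to a registered review protocol in S4 Appendix, and promises adaptation to each database with an inventory of the criteria used. Country lists and subject headings are commonly left to such a document. Subject indexing, affiliation fields or full-text matching may pick up country-only records, and checking citations and bibliographies is a recognised route to studies that a string misses. Study location is to be extracted and interventions described by setting, so an imbalance would be visible. Meta-analysis is only to be considered if reporting allows, and the recommendations are for South Africa, which softens the effect of a tilt in that direction.

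Much of this stands as a limit on certainty and size. It does not remove the point. The string is a rule the article states, twice, and not a detail it leaves out. Adaptation to each database is not confined to syntax, but it does not promise country names. A second reviewer running the same string would get the same misses. Bibliography review starts from the records already found, so it starts from any tilt present in them. The sample size section defers inclusion criteria to the review protocol; it does not say that the search terms there differ. Extracting location shows which countries are present, but not which eligible studies were never retrieved.

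A reader might infer more: that country-only studies are in fact lost, that South African studies always pass, and that they will be over-represented by a known amount. The documents do not support that. Recovery through other routes is possible, bare Africa does not match South African as a whole word, and the fractions behind any share are assumed.

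**Conclusion.** The point holds as a risk built into the printed string. Run as text, it is narrower than the scope stated in the same table, and it favours records containing the words South Africa. That follows from the wording alone.

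How many eligible studies would be lost, and how far the retrieved set would lean, cannot be determined from the documents. The shares above indicate scale under assumed inputs and are not estimates. Nothing in the article shows that intervention effects differ by country, so no bias in a pooled effect can be claimed; what is at stake is the completeness of the regional evidence. If S4 Appendix already contains country terms, the remaining defect is that Table 1 does not match it.

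**What to change.** Before the final searches, extend the geographic block of Table 1, joined by OR with the existing terms, to include:

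- the names, and former names, of all sub-Saharan countries;
- African, or a truncation that covers both noun and adjective;
- each database's own regional subject headings.

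Use the same country list in every database, and test the block against a small set of studies already known to be eligible, chosen from several countries. If S4 Appendix already has these terms, bring Table 1 and the running text into line with it and say so.

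The cost is a larger number of titles and abstracts for the same reviewers to screen, and an updated registration entry. No other part of the Phase IV analysis needs to change.
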